## Background

Antimicrobial resistance (AMR) is a global health emergency, with a significant negative impact on health and socioeconomic development, in particular in low-resource settings. A major driver of AMR emergence is antibiotic use, where community-level antibiotic consumption, in addition to individual-level usage, has been associated with an increased risk of individual community members acquiring AMR bacteria [1]. As a result of difficult or delayed access to hospitals and formal health centres in many low-resource communities, self-medication with antibiotics from formal and informal medicine outlets, frequently without medically qualified staff, is widespread [2]. In sub-Saharan Africa, over two thirds of visits to community medicine stores may result in dispensing prescription-free antibiotics [3]. In the absence of a clinical or microbiological diagnosis, and with antibiotic sales a major source of revenue, community medicine outlets often dispense antibiotics without a clear rationale. Importantly, these antibiotic courses frequently consist of antibiotics classified by WHO as ‘Watch’ antibiotics, which should be restricted to specific indications due to their higher AMR potential [4, 5].

At the same time, healthcare providers or dispensers in medicine outlets may be faced with a strong demand from their communities for antibiotic treatments which, in the absence of a clinical assessment, risks to result in unnecessary or inappropriate antibiotic dispensing and usage. One RCT in India evaluated a bundle intervention targeting informal medicine outlets with an intensive multi-topic training programme over 9 months and found it improved correct clinical case management [6]. Unfortunately, a direct effect on the frequency of antibiotic use could not be demonstrated. The intervention, however, only targeted informal medicine outlets and did not seek to address the demand for antibiotics from the community.

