### Study setting and population

Health demographic surveillance sites (HDSS) exist in Nanoro district, Burkina Faso, and Kimpese district, DRC where trusted long-term contacts have been built with the communities. This provides a fertile environment for high-quality studies [9]. The HDSS in Nanoro was established in 2009 and currently includes a population of about 60,000 people, living in 24 villages. 16 of these villages have a primary care health facility, to which a community pharmacy store is linked. The HDSS in Kimpese was established in 2018 and included a population of about 170,000. In the central town of each HDSS (Nanoro and Kimpese), there is a public district referral hospital, with a clinical and a research laboratory attached. Both HDSS have quality-controlled bacterial culture and antibiotic susceptibility testing capacity installed at the district hospital level. Experienced social science teams are integrated in both HDSS.

Populations in these sites are well-characterised in terms of demographics, socio-economic status, healthcare utilisation and access-to-water and hygiene parameters. Essential demographic information is updated on a continuous basis through village-based reporters, while structural information is updated during annual rounds, as well as during dedicated study visits. Baseline demographic and health indicators of households are collected at 4–6 monthly intervals, and clinical microbiology surveillance has been established in the district referral hospitals [10, 11].

Pilot studies in the HDSS of both settings, confirmed that health centres (66% in Nanoro, 68% in Kimpese), private clinics (none in Nanoro, 4% in Kimpese), community pharmacies (17% in Nanoro) and informal medicine vendors (16% in Nanoro, pharmacies and informal vendors 18% in Kimpese) were the main sources of antibiotics [12, 13]. Frequent consumption of non-prescribed antibiotics was reported by community members exiting from these local medicine stores, with a significant proportion consisting of Watch antibiotics (20% in Nanoro [14] and 24% in Kimpese [13]). Furthermore, purchased antibiotic courses were frequently underdosed or interrupted [13, 14].

Implementing the behavioural intervention bundle will not require alteration to usual care pathways and these will continue for both trial arms.

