### Sample size

The sample size is based on the primary outcome. Including in each setting 22 clusters, with per cluster 100 patients to be interviewed upon exiting a medicine store, a frequency of Watch antibiotic use of 24% in DRC [13], and assuming an estimated intraclass coefficient of 0.05, a cluster level correlation (rho_c_) of 0 (conservative), subject level correlation (rho_s_) of 0 (different subjects at baseline and at 12 months), our study has 80% power to observe a 40% reduction in Watch antibiotic use.

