### Data collection

Data collection will be done twice: first pre-intervention, and repeated a year later, post-intervention, to account for seasonality in antibiotic use, health care seeking behaviour and in WaSH practices (see also timeline, Fig. 2):Repeated patient visit exit surveys: After completing a healthcare visit, patients and parents of paediatric patients (regardless of whether they received an antibiotic) will be surveyed, using a structured questionnaire, on: symptoms, quantity of antibiotics dispensed/purchased by group of antibiotics if any, dose and duration of antibiotic treatment (including potential up/downscaling), mode of administration, number of antibiotics and antimalarials used concomitantly (including reasons). These surveys will be carried out pre- and post-intervention at identified medicine stores in intervention and control clusters.Repeated visits by simulated patients are the gold standard to evaluate patient management and the appropriateness of antibiotic dispensing in medicine outlets: they present at the medicine outlet and answer to questions in a standardised way (trained before the visit) to mimic clearly outspoken medical conditions for which the indication to treat or refer cannot be debated [25]. Simulated patients are blinded whether the outlet they visit received intervention input or not. Visits are unannounced to avoid that providers adapt their behaviour during those visits to be more desirable when observed, a so-called Hawthorne effect. The most suitable tracer conditions will be identified during the formative research stage [6]. Case management is evaluated using a standardised scoring grid evaluating clinical assessment and anamnesis, actions taken and medicine dispensing during or following the visitRepeated household surveys: during repeated household visits, pre- and post-intervention, we will record potential factors associated with AMR transmission (in particular, hygiene and infection control practices). Stool samples will be collected from a selected number of household participants for analysis of the presence of Enterobacteriaceae and their antibiotic susceptibility.Rodents are an abundant and diverse group of small mammals, with several species living in close contact with humans and livestock, making them a relevant group for environmental surveillance of AMR [26]. To assess their potential in environmental AMR surveillance, rodents will be collected for stool sampling for similar analysis of the presence of Enterobacteriaceae and their antibiotic susceptibility twice, once during the dry season, once during the wet season, at different distances from human habitation, with a focus on the peridomestic species that are common in the study area (*Mus musculus*, *Mastomys natalensis*).Following the implementation of the interventions, a qualitative process evaluation among providers and community members is planned to understand perceptions and intended and potentially unintended impact of the evaluation in a selection of the intervention clusters using focus groups and individual interviews with key stakeholders.

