
### Analysis

The effect evaluation will use standard experimental methods and will make use of multilevel statistical models (to account for clustering within villages and households), including time*intervention interactions. The population’s socio-demographics, socio-economic status, healthcare use and health behaviour are regularly recorded during scheduled HDSS rounds, which will allow subgroup analyses of the effect of the intervention.

Based on the exit interviews, the proportion of primary care or medicine outlet visits resulting in dispensing of Watch antibiotic courses will be estimated, adjusted for clustering, in the intervention and in the control groups before and 12 months after the start of the intervention. Antibiotics will be grouped as Access, Watch or Reserve (AWaRe) according to WHO’s 2019 AWaRe classification. Patients’ antibiotic treatment dose, dosage, duration, mode of administration and uptake will be assessed, to determine the Defined Daily Doses (DDD) each treatment course accounts for. We assess for each treatment course whether the treatment is underdosed, based on the 2022 WHO AWaRe Antibiotic Book. A case management score is deducted using the scoring grid to be completed after each simulated patient visit. The change in frequency of Watch antibiotic use and in mean case management score before and after the intervention (months 0 and 12) will be compared to that during the same period in the control areas. We will determine risk differences and risk ratios, which will be adjusted for socio-economic indicators and other potential confounding factors. Linear and non-linear regression models will be used to estimate the effect and carry out subgroup analyses.

Stool samples will be cultured on selective CHROMagar™ plates and species identified. If *E. coli* and/or *Salmonella* isolates are detected, they will be typed and antibiotic susceptibility testing done according to CLSI guidelines for pathogen-antibiotic indicators and for ESBL, if the minimal inhibitory concentration for ceftriaxone or ceftazidime is above 1 mg/L.

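### The 24% planning rate is described elsewhere as a Watch share of antibiotics, whereas the outcome is a share of all visits; the lower 20% reported for Nanoro is not used

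*Protocol article*

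**What the plan says.** The Sample size section of the protocol article fixes the clusters by country: "Including in each setting 22 clusters, with per cluster 100 patients to be interviewed upon exiting a medicine store". It then takes "a frequency of Watch antibiotic use of 24% in DRC [13"], an ICC of 0.05 and zero cluster-level and subject-level correlations over time, and states 80% power for a 40% reduction in Watch use. No rate is given for Burkina Faso and no significance level is stated.

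Study setting and population uses the same source for the same site, but says what the figure is a share of. It speaks of non-prescribed antibiotics reported by people leaving medicine stores, "with a significant proportion consisting of Watch antibiotics (20% in Nanoro [14] and 24% in Kimpese [13"].

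The Analysis section defines the exit-interview outcome as "the proportion of primary care or medicine outlet visits resulting in dispensing of Watch antibiotic courses". Data collection confirms the denominator: patients are surveyed "regardless of whether they received an antibiotic".

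**The concern.** Three statements have to agree and do not: what the 24% measures, what the outcome measures, and which country the rate describes. A Watch share among antibiotics and a Watch share among visits coincide only in special cases, for example when every visit yields exactly one antibiotic. If some visits yield none, the per-visit rate is probably below 24%.

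Separately, the cluster number is set for each setting, while the rate entered is the higher of the two that the article reports.

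Both points act in the same direction. At a fixed relative reduction and a fixed ICC, a lower baseline rate means a smaller absolute difference and less power. At stake is how a null result is read, especially in one country: it could be set against a claimed 80% power that the design does not have for this outcome.

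**Working it through.** **Inputs.** From Sample size: 22 clusters per setting, 100 patients per cluster, ICC 0.05, both correlations over time 0, 40% relative reduction. From Study design: 1:1 allocation, so 11 clusters per arm per setting. From Study setting and population: 24% (Kimpese, DRC) and 20% (Nanoro, Burkina Faso). Assumed: two-sided 5% level, normal approximation.

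**Effective size.** Design effect = 1 + 99 × 0.05 = 5.95. Effective n per arm = 1100 / 5.95 = 184.9 in one setting, or 2200 / 5.95 = 369.7 with both settings pooled.

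**Formulas.** p1 is the control rate, p2 = 0.6 × p1, Δ = p1 − p2, and p̄ is their mean.

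- Follow-up comparison: power = Φ[(Δ − 1.96 × SE0) / SE1], with SE0 = √[2p̄(1 − p̄)/n] and SE1 = √{[p1(1 − p1) + p2(1 − p2)]/n}.
- Time-by-intervention contrast, correlations 0: power = Φ[Δ/SE − 1.96], with SE = √{[3p1(1 − p1) + p2(1 − p2)]/n}.

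**The plan's own figure first (24% to 14.4%, one setting).**

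- Follow-up: Δ = 0.096, SE0 = 0.0410, SE1 = 0.0407, power 65%.
- Interaction: SE = 0.0602, power 36%.

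The stated 80% is not reproduced. Pooling both settings at 24% gives 91% and 62%, which is not 80% either. That is a separate difficulty, and it is the starting level for what follows.

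**Nanoro's reported rate (20% to 12%).**

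- Follow-up, one setting: Δ = 0.080, SE0 = 0.0381, SE1 = 0.0379, power about 56%.
- Interaction, one setting: SE = 0.0563, power 30%.

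| Control rate | One setting: follow-up / interaction | Pooled: follow-up / interaction |
|---|---|---|
| 24% | 65% / 36% | 91% / 62% |
| 20% | 56% / 30% | 84-85% / 52% |

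The pooled row at 20% applies that rate in both countries.

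**Denominator, illustration only.** The share of visits that yield an antibiotic at these sites is not in the article. The Background says that in sub-Saharan Africa "over two thirds of visits to community medicine stores may result in dispensing prescription-free antibiotics", which is a regional and hedged figure for medicine stores. With one antibiotic per visit and the ICC held at 0.05, the DRC per-visit rate would be:

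- share 0.8: 0.24 × 0.8 = 19.2%, follow-up power about 54%, interaction 28%;
- share two thirds: 0.24 × 2/3 = 16%, follow-up power about 45%, interaction 24%.

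**Sensitivity to the ICC.** Suppose the between-cluster coefficient of variation implied by 24% and ICC 0.05 is held fixed instead. Its square is 0.05 × 0.76 / 0.24 = 0.158, so the ICC at 20% is 0.158 × 0.20 / 0.80 = 0.040. Follow-up power per setting is then about 64% at 20% and 62% at 16%, so most of the fall disappears.

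**The case against.** - **The shortfall at 24% is a different problem.** This stands. The gap between 80% and 65% (or 36%) has nothing to do with the denominator or with Nanoro. The loss that follows from the article's own figures is 65% to 56%, or 36% to 30%.
- **The power claim may be for the whole study.** A reader might infer that 80% is promised in each country. The text attaches the setting to the cluster count and the power to the study. On a pooled follow-up reading, 20% in both countries still gives about 84-85%, so Nanoro's rate alone would not break the claim. It does not rescue the interaction contrast, which the Analysis section names: 52% at 20%, and only 62% at 24%.
- **The source may have measured 24% per visit.** This cannot be checked from the article. The description in Study setting and population would then be misworded. The sections would still need reconciling, and the unused Nanoro figure would remain.
- **Multiplying by an antibiotic share is not an identity.** This stands. Data collection records the number of antibiotics used concomitantly, and with several per visit the per-visit Watch rate can exceed the product. The pilot figures also concern non-prescribed antibiotics from medicine stores, while the outcome covers primary care visits too; the direction of that mismatch is unknown.
- **Burkina Faso worst affected.** A reader might infer this from 20% against 24%. It needs equal antibiotic shares in both countries, which the article does not give. With shares of 0.8 in Nanoro (16%) and 0.5 in Kimpese (12%), the order reverses.
- **Little can change.** Clusters are fixed and implementation began in February 2023. The correction therefore alters what the trial reports about its power, not its design.

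**Conclusion.** The point holds as an inconsistency in the planning rate. The 24% is described as a share of non-prescribed antibiotics, the outcome is a share of all visits, and the lower rate reported for one of the two countries is left out.

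The size that rests on the article's figures, with a two-sided 5% level assumed and the stated ICC kept, is a fall in per-setting power from about 65% to about 56% at follow-up, and from 36% to 30% for the interaction. Any further loss from the denominator is likely but not quantifiable here: it depends on the antibiotic share of visits, the antibiotics per visit and the ICC at the lower rate. The 54% and 45% for DRC are illustrations, not estimates. The documents support neither a ranking of the two countries nor the reading that 80% was explicitly promised in each.

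**What to change.** Reconcile Study setting and population, Sample size and Analysis on what the 24% is a share of. Then restate the power from the per-visit Watch proportion in the baseline exit surveys, by country. Say whether the figure is per setting or pooled, and whether it is for the follow-up comparison or the time-by-intervention contrast. State the significance level, and preferably take the ICC from the same data.

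If the Watch share of antibiotics is the intended outcome, say so in Analysis and reduce the analysed number per cluster from 100 to the visits that yielded an antibiotic.

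The cost is a recalculation and a few changed sentences. Study design says that allocation was concealed until baseline data were available, so the data should be in hand, and no extra enrolment is needed. The downside is that the stated power will probably look less favourable.

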### Data collection

Data collection will be done twice: first pre-intervention, and repeated a year later, post-intervention, to account for seasonality in antibiotic use, health care seeking behaviour and in WaSH practices (see also timeline, Fig. 2):Repeated patient visit exit surveys: After completing a healthcare visit, patients and parents of paediatric patients (regardless of whether they received an antibiotic) will be surveyed, using a structured questionnaire, on: symptoms, quantity of antibiotics dispensed/purchased by group of antibiotics if any, dose and duration of antibiotic treatment (including potential up/downscaling), mode of administration, number of antibiotics and antimalarials used concomitantly (including reasons). These surveys will be carried out pre- and post-intervention at identified medicine stores in intervention and control clusters.Repeated visits by simulated patients are the gold standard to evaluate patient management and the appropriateness of antibiotic dispensing in medicine outlets: they present at the medicine outlet and answer to questions in a standardised way (trained before the visit) to mimic clearly outspoken medical conditions for which the indication to treat or refer cannot be debated [25]. Simulated patients are blinded whether the outlet they visit received intervention input or not. Visits are unannounced to avoid that providers adapt their behaviour during those visits to be more desirable when observed, a so-called Hawthorne effect. The most suitable tracer conditions will be identified during the formative research stage [6]. Case management is evaluated using a standardised scoring grid evaluating clinical assessment and anamnesis, actions taken and medicine dispensing during or following the visitRepeated household surveys: during repeated household visits, pre- and post-intervention, we will record potential factors associated with AMR transmission (in particular, hygiene and infection control practices). Stool samples will be collected from a selected number of household participants for analysis of the presence of Enterobacteriaceae and their antibiotic susceptibility.Rodents are an abundant and diverse group of small mammals, with several species living in close contact with humans and livestock, making them a relevant group for environmental surveillance of AMR [26]. To assess their potential in environmental AMR surveillance, rodents will be collected for stool sampling for similar analysis of the presence of Enterobacteriaceae and their antibiotic susceptibility twice, once during the dry season, once during the wet season, at different distances from human habitation, with a focus on the peridomestic species that are common in the study area (*Mus musculus*, *Mastomys natalensis*).Following the implementation of the interventions, a qualitative process evaluation among providers and community members is planned to understand perceptions and intended and potentially unintended impact of the evaluation in a selection of the intervention clusters using focus groups and individual interviews with key stakeholders.

### Analysis

The effect evaluation will use standard experimental methods and will make use of multilevel statistical models (to account for clustering within villages and households), including time*intervention interactions. The population’s socio-demographics, socio-economic status, healthcare use and health behaviour are regularly recorded during scheduled HDSS rounds, which will allow subgroup analyses of the effect of the intervention.

Based on the exit interviews, the proportion of primary care or medicine outlet visits resulting in dispensing of Watch antibiotic courses will be estimated, adjusted for clustering, in the intervention and in the control groups before and 12 months after the start of the intervention. Antibiotics will be grouped as Access, Watch or Reserve (AWaRe) according to WHO’s 2019 AWaRe classification. Patients’ antibiotic treatment dose, dosage, duration, mode of administration and uptake will be assessed, to determine the Defined Daily Doses (DDD) each treatment course accounts for. We assess for each treatment course whether the treatment is underdosed, based on the 2022 WHO AWaRe Antibiotic Book. A case management score is deducted using the scoring grid to be completed after each simulated patient visit. The change in frequency of Watch antibiotic use and in mean case management score before and after the intervention (months 0 and 12) will be compared to that during the same period in the control areas. We will determine risk differences and risk ratios, which will be adjusted for socio-economic indicators and other potential confounding factors. Linear and non-linear regression models will be used to estimate the effect and carry out subgroup analyses.

Stool samples will be cultured on selective CHROMagar™ plates and species identified. If *E. coli* and/or *Salmonella* isolates are detected, they will be typed and antibiotic susceptibility testing done according to CLSI guidelines for pathogen-antibiotic indicators and for ESBL, if the minimal inhibitory concentration for ceftriaxone or ceftazidime is above 1 mg/L.

A selection of ESBL-producing *E. coli* isolates will be sequenced. DNA will be extracted and prepared for whole genome sequencing (WGS) using Illumina technology available through the Cancer Research UK facility. The WGS data will be bioinformatically assessed for quality and analysed to confirm species and sequence type per isolates. Furthermore, the genetic content of AMR genes and the presence of plasmid replicons will be determined. In-depth comparative genomics approach will be used to assess relatedness between isolates through reconstruction of the maximum likelihood phylogenies per species/sequence type, with their representative metadata including AMR data. From this, we can assess whether isolates belong to different clades or whether the isolates are interspersed, suggesting ongoing transmission between reservoirs. We will use a Bayesian approach (using BEAST [27]) to estimate transmission events.

We will also use these data to fit Markov models to longitudinal household data derived from repeated stool samples. This will enable estimation of the rate of person-to-person transmission within households, the rate of loss of detectable carriage within individuals, and the association of these rates with the study intervention and baseline household covariates. We will perform this analysis both at the level of the AMR gene and, where typing data permits, at higher levels. Individuals will be classified as non-carriers or carriers of AMR pathogens or genes, and intervention exposure is assumed to alter transition probabilities between states. Based on the results of the phylogenetic comparison of AMR bacterial populations, we will explore different hypotheses related to the relative importance of an environmental acquisition source, by considering different model structures allowing for the presence or absence of environmental acquisition.

Qualitative data will be analysed using NVivo following transcription of focus groups and individual interviews to identify dominant themes and explore perceptions.

No specific analysis is foreseen related to non-adherence or missing data as the intervention is at community level, as well as collection of pre and postintervention data. A community cannot not adhere or go missing; the intervention and data collection before and after will target those community members and providers who are present and willing to participate.

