## Methods

### Study design

In a cluster randomised trial, we will evaluate if a year-long behavioural intervention bundle in a rural setting in Burkina Faso (Nanoro district) and in the Democratic Republic of Congo (DRC) (Kimpese district) has a superior outcome on a range of standardised AMR and WaSH indicators in intervention and control villages. Controlled measurements of antibiotic use (patient surveys), patient management (mystery patients) and water-sanitation-hygiene (household surveys) will be collected in the same season before and after. In each setting, eligible villages and town neighbourhoods (clusters) will be randomly allocated to intervention or no intervention (control). Randomisation is in two strata per site. In Nanoro, strata distinguished villages with primary health centre and those without (only formal or informal medicine outlets). In Kimpese, strata distinguished peri-urban neighbourhoods of rural villages. For each stratum, clusters (villages or neighbourhoods) are randomised 1:1 as intervention or control. A random number between 0 and 1 is given to each cluster using the RAND() function in Excel by a local data manager not involved in the trial. Half of the cluster in each of both strata, those with the higher numbers, are selected as intervention clusters; the other half, with the lower numbers, as control clusters. Allocation of villages to intervention or control was concealed until all had been recruited and baseline data available.

By randomising communities rather than individuals, contamination of intervention and no intervention should be maximally avoided, as supported by pilot studies in the DRC that observed that >80% of social contacts were with people in the same village or neighbourhood (manuscript in preparation). A steering committee consisting of the PIs of all 7 participating institutes will meet at least annually to discuss progress, and at least annually full consortium meetings will be organised with options for on-line participation.

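### The clustering levels named for the time-by-intervention model leave out the village-by-period variation that the sample size assumes, so fitted literally the test of the change in Watch use has type I error well above 5%

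*Protocol article*

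**What the plan says.** The Analysis section of the protocol article opens with one description of the effect model: "multilevel statistical models (to account for clustering within villages and households), including time*intervention interactions". It then sets the primary comparison for antibiotic use as the before-after change in Watch use in the intervention arm against the change over the same period in the control arm. For the exit interviews it adds only that proportions are adjusted for clustering. No period-specific village term is named, and none is ruled out.

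The Sample size section is more specific about correlation. On size it says: "Including in each setting 22 clusters, with per cluster 100 patients to be interviewed upon exiting a medicine store". The starting level it plans with is "a frequency of Watch antibiotic use of 24% in DRC". The correlations are an ICC of 0.05, then "a cluster level correlation (rho_c_) of 0 (conservative"), and a value of 0 at subject level because different people are interviewed in the two rounds.

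The Data collection section says of the exit surveys: "These surveys will be carried out pre- and post-intervention at identified medicine stores in intervention and control clusters". The patients are therefore sampled at outlets within villages.

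**The concern.** The two sections imply different variance structures. Setting rho_c = 0 with a non-zero ICC means that a village's baseline level tells nothing about its level a year later, so all village variance belongs to the village in a given round. Staff turnover at an outlet or a change in stock would produce such variation. The levels named in the Analysis section are village and household. A village effect common to both rounds drops out of a before-after change, so it cannot protect the interaction test. A household effect does not help either, because a village-period shock is shared by everyone interviewed in that village in that round.

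A statistician who followed the sentence literally would treat village drift as independent patient-level noise. The standard error of the effect on Watch use would be too small, and an ineffective intervention could be reported as effective.

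**Working it through.** **Inputs.** From Sample size: 22 clusters per country, p = 0.24, ICC = 0.05, rho_c = 0, rho_s = 0. From Study design: "clusters (villages or neighbourhoods) are randomised 1:1 as intervention or control", so 11 per arm. Assumed: m = 100 patients per village per round (the text says "with per cluster 100 patients to be interviewed upon exiting a medicine store" without saying whether this is per round or in total), and two-sided alpha of 0.05 (none is stated). Strata are ignored.

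**The plan's own figure.** The statement is "our study has 80% power to observe a 40% reduction in Watch antibiotic use", that is 0.24 to 0.144.
- Design effect: 1 + 99 × 0.05 = 5.95. Effective n per arm: 11 × 100 / 5.95 = 184.9.
- z = [0.096 × √184.9 − 1.96 × √(2 × 0.192 × 0.808)] / √(0.24 × 0.76 + 0.144 × 0.856) = (1.305 − 1.092) / 0.553 = 0.386, which gives 65% power for a post-only or baseline-adjusted comparison.
- A difference in changes at rho_c = 0 doubles the variance (effective n 92.4), which gives 38%.
- With 44 pooled clusters the figures are 91% and 65%.

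The stated 80% is not reproduced. That is a separate matter, and the type I error below does not depend on it.

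**Type I error with a village intercept only.** Write a village's result in a round as a stable village effect plus a village-period effect plus sampling error. The stable effect cancels from the change. In units of p(1 − p), scaled by m/2, the variance of a village's change is

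V_true = (1 − ICC) + m × ICC × (1 − rho_c).

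The intercept-only model uses approximately the residual variance left after the stable village part is removed:

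V_model ≈ 1 − ICC × rho_c.

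The actual type I error is 2 × [1 − Φ(1.96 × √(V_model / V_true))].

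| rho_c | V_true (m = 100) | V_model | Ratio | Type I error, m = 100 | V_true (m = 50) | Type I error, m = 50 |
|---|---|---|---|---|---|---|
| 0 | 0.95 + 5.00 = 5.95 | 1.000 | 5.95 | 42% | 3.45 | 29% |
| 0.5 | 0.95 + 2.50 = 3.45 | 0.975 | 3.54 | 30% | 2.20 | 19% |
| 0.8 | 0.95 + 1.00 = 1.95 | 0.960 | 2.03 | 17% | 1.45 | 11% |
| 0.9 | 0.95 + 0.50 = 1.45 | 0.955 | 1.52 | 11% | 1.20 | 8% |
| 1 | 0.95 | 0.950 | 1.00 | 5% | 0.95 | 5% |

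The m = 50 columns apply if the 100 patients cover both rounds; simulation puts the 19% entry at 19 to 20%. At rho_c = 0 and m = 100 the standard error is too small by a factor of about √5.95 = 2.4. The number of clusters does not enter the formula, so pooling countries cannot repair it. At rho_c = 0 and m = 100, an ICC of 0.02 still gives 26% and 0.01 gives 17%.

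**Simulation checks (m = 100, ICC 0.05, no effect).**
- Linear model, 22 clusters, 20,000 trials per setting: 42.2%, 29.6%, 17.4%, 11.4% and 4.9% at rho_c = 0, 0.5, 0.8, 0.9 and 1.
- Logistic random-intercept model, 1,000 trials per setting: 44.8%, 28.3% and 18.1% at rho_c = 0, 0.5 and 0.8 with 22 clusters; 43.6%, 30.5% and 18.0% with 44.
- t-test on village-level changes in the same 1,000-trial runs: 5.4%, 6.1% and 5.0% with 22 clusters; 3.8%, 5.9% and 5.6% with 44. These agree with 5% within simulation error.

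**The case against.** The strongest reply is that the Analysis sentence is a generic line in a condensed article. It never says random intercept, never says that village and household are the only terms, and excludes nothing. A multilevel model with a random village time effect fits the same words, and the exact random-effects structure is commonly left to a SAP, which is not shown. This stands. A reader might infer that the planned primary test has a 42% false-positive rate; the documents do not support that as a fact about the plan, only as the consequence of one literal reading.

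It is also fair that rho_c = 0 is a bound the authors label conservative, not a claim that villages have no stable level. So 42% is the upper end, and the documents give no empirical value of rho_c.

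Two further inferences should be resisted. Season is not a cause of the drift, because both rounds are placed in the same season by design. Nor is household a wrong level throughout: changes in community carriage are also listed as a primary outcome and come from household participants. The mismatch concerns only the exit survey.

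What the reply does not remove is that the article chose to name the levels, and those levels omit the variance component on which its own sample size rests.

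**Conclusion.** The point holds as a conditional mismatch between two sections. If the named levels are fitted as random intercepts and are the whole structure, the test of the change in Watch use exceeds its nominal 5% at every rho_c below 1. With ICC 0.05 and 100 patients per village per round, the error runs from 11% at rho_c = 0.9 to 42% at the planning bound of 0. If the 100 covers both rounds, it runs from 8% to 29%. The result rests on the stated ICC, the reading of cluster size, a two-sided 5% level and a Wald test. It does not establish that the trial will be analysed this way.

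**What to change.** State in the Analysis section that the exit-survey model for Watch use includes a village-by-period random effect (or a random village time effect) with a small-sample correction such as Kenward-Roger, Satterthwaite or a t reference on clusters minus 2. Alternatively, analyse village-level changes with a t reference or a permutation test. For exit surveys name outlet within village as the lower level, and keep household for the household-survey and stool-carriage outcomes.

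This takes a sentence or two and no new data. The cost is wider confidence intervals. At rho_c = 0, a valid comparison of changes has about 33 to 38% power for 24% to 14.4% with 22 clusters, against about 61 to 65% if follow-up is compared with or without adjustment for baseline. The choice between those two contrasts should therefore be made at the same time. If the SAP already specifies such a model, a reference to it is enough.
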